### Duration of study participation

Participants will be involved for approximately 1 month, including screening, treatment, and follow-up. After consent, patient participation in the intervention phase will last 72 hours for active treatment. The follow up for determination of outcome and duration of mechanical ventilation will occur at 1-month post-treatment. Additional data will be collected via chart review.

### Total number of subjects and sites

This single-site study aims to recruit and randomize 20 patients. It is expected that up to 30 subjects may be consented in order to produce 20 randomized & evaluable subjects.

### Core temperature modulation

Core temperature control and warming will be performed with a commercially available esophageal heat exchange device (ensoETM, Attune Medical, Chicago, IL). This device is currently used world-wide for various patient temperature management goals, including post-cardiac arrest therapeutic hypothermia [53–56], warming of burn patients [57], warming general surgical patients [58], cooling traumatic brain injury [59], cooling heat stroke [60], and the treatment of central fever [61,62]. The device is a multi-chambered silicone tube placed in the esophagus and connected to a heat exchanger to provide heat transfer to or from a patient (video available at https://vimeo.com/306506411). Modulation and control of the patient’s temperature is achieved by adjusting setpoint on the external heat exchanger, which in turn controls the circulating water temperature. Two lumens of the device connect to the external heat exchanger, while a third central lumen provides stomach access for gastric decompression or tube feeding. It is a single-use, disposable, non-implantable device with an intended duration of use of 72 hours or less.

### Intervention regimen

Patients who are randomized to core warming will have the esophageal heat transfer device placed in the ICU or other treatment area where patient is undergoing mechanical ventilation. The device will remain in place until the study is completed (72 hours). The device will be set to 42°C for the duration of the study period. It is expected that patient temperature will increase from baseline by 1°C to 2°C, but due to ongoing heat loss from the patient, the expected maximum patient temperature is below 39°C. The time course of illness of COVID-19 is such that patients often no longer have fever by the time of mechanical ventilation [41]. If patient temperature increases above this range and reaches 40°C, the device will be set to an operating temperature of 40°C, thereby preventing any further increase in patient temperature. Patient temperature will be followed at intervals per standard of care in the intensive-care setting for mechanically ventilated patients (typically hourly).

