### Study objectives

The purpose of the proposed pilot study is to determine if core warming improves respiratory physiology of mechanically ventilated patients with COVID-19, allowing earlier weaning from ventilation, and greater overall survival.

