### Study intervention and monitoring

Participants who have a signed research study consent form (via surrogate or legally authorized representative) will be randomized in a 1:1 fashion to core warming or to standard of care (standard temperature management and treatment). The esophageal heat transfer device will be used according to FDA 510(k) labeling (for patient warming). Patient temperature measurements will be collected for both the device and standard-of-care arms during the study period (up to 72 hours). Device placement will be performed using standard protocol per instructions for use. The esophageal heat transfer device will be set to 42°C temperature after initial placement, and maintained at 42°C for the duration of treatment. All patients will have usual standard of care labs, vital signs, and imaging for patients in critical condition undergoing mechanical ventilation in the ICU. Specific parameters to be measured include PaO2 at regular intervals appropriate for patients undergoing mechanical ventilation, and FiO2 at the time of obtaining blood gases for PaO2 measurement, to allow calculation of P/F ratio.

Control group patients will be managed as per standard of care currently utilized in the ICU, which will include the use of other methods of temperature management as warranted. This would include warming with a forced air blanket only in hypothermic patients (core temperature < 36°C) or antipyretic therapy for febrile patients, as requested by the treating physician. Episodes of hypothermia are infrequent and transient in this population, and the current standard of care generally utilizes a permissive approach to fever (allowing patients to remain mildly febrile) which will continue in the control group without modification (no intentional elevation of temperature will be provided in the control group).

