### Primary study endpoints

*The primary endpoint of this study will be*:

Viral load measured in lower respiratory tract sample 72 hours after initiation of core warming

*Secondary study endpoints include*:

PaO2/FiO2 ratio 24, 48, and 72 hours after initiation of core warmingDuration of mechanical ventilationDuration of ICU and hospital stayPatient mortality

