### Sample size and power determination

Based on a prior study in patients with sepsis, a maximum temperature of 38.3°C to 39.4°C was associated with survival (aHR 0.61 [95% CI, 0.39–0.99]) [29]. However, the effect of warming specific to COVID-19 patients remains uncertain, and as such, it is not possible to accurately perform a power calculation for this pilot study. It is believed that a total of 10 patients for each group will yield the sufficient pilot data to make an appropriate conclusion regarding the potential utility of core warming in reducing viral load, improving pulmonary physiology, reducing mechanical ventilation duration, and increasing patient survival. It is anticipated that data from this pilot study can be used for planning future larger studies.

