### Statistical methods

We will utilize standard measures to report outcomes and measure differences between groups. Specifically, we will use descriptive statistics, including mean (standard deviation) and median (interquartile range). Kaplan-Meier plots of important time to event outcomes and measures will be produced. Normality will be assessed using histograms and the Kolmogorov–Smirnov test. Formal hypothesis testing is not planned for this pilot feasibility study.

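### The 48- and 72-hour P/F comparison can lose patients through extubation or death, and treatment may affect both, so the effect size the pilot is meant to supply may be distorted in an unknown direction.

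*Protocol article*

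**What the plan says.** - **Endpoint times.** Primary study endpoints (Protocol article) lists "Viral load measured in lower respiratory tract sample 72 hours after initiation of core warming" as primary, and P/F ratio at 24, 48 and 72 hours as secondary.
- **Source of P/F.** Study intervention and monitoring says: "Specific parameters to be measured include PaO2 at regular intervals appropriate for patients undergoing mechanical ventilation", with FiO2 recorded alongside the blood gas. Data collection adds that data come by chart review from routine care. The article describes no study-driven blood gas.
- **Who is analysed.** Subject population for analysis keeps patients who were enrolled, randomised and completed in the study. It does not define completion.
- **Effects sought.** Study objectives gives the purpose as better respiratory physiology, "allowing earlier weaning from ventilation, and greater overall survival". Duration of ventilation and mortality are separate secondary endpoints.
- **Entry.** Screening admits patients ventilated for three days or less.
- **Device time.** Intervention regimen says "The device will remain in place until the study is completed (72 hours" and gives no exception for extubation. Core temperature modulation describes an intended use of 72 hours at most. Study intervention and monitoring also treats 72 hours as the upper limit of the study period.
- **Lower-tract specimens.** Data collection accepts tracheal aspirate or sputum.
- **Use of the results.** Study endpoints says the estimates are for sizing definitive studies. Statistical methods says "Formal hypothesis testing is not planned for this pilot feasibility study".

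**The concern.** The P/F endpoint is set at fixed hours for everyone, but its values come from a care pathway that applies while the patient is ventilated. Suppose a patient is extubated at 40 hours. Nothing in the article secures a 48- or 72-hour blood gas for that patient, and it is unclear whether the patient counts as having completed. A patient who dies at 40 hours certainly has no later value.

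Both events are effects that the trial hopes to change. The patients who still have a P/F at 72 hours are then a selected group in each arm, and the selection can differ between arms. A mean difference among them no longer compares the randomised groups. That matters in a pilot without hypothesis tests, because the effect estimate and its SD are what the next trial will be built on.

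**Working it through.** **No figure of the plan to reproduce.** The article gives "a total of 10 patients for each group will yield the sufficient pilot data" and states that "it is not possible to accurately perform a power calculation for this pilot study". It gives no P/F mean, SD, effect, extubation rate or early death rate. Every input below is an assumption, chosen to show how the size of the problem varies.

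**How often the situation would arise.** If a proportion q of patients is extubated before 72 hours, the chance that at least one of 20 is affected is 1 − (1 − q)^20.
- q = 5%: 1 − 0.95^20 = 64%
- q = 10%: 1 − 0.90^20 = 88%
- q = 20%: 1 − 0.80^20 = 99%

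**Size if extubation removes the high values.** Assume 72-hour P/F is normal with SD 60 and mean 180 (control) or 220 (warming), so the true difference is 40. Assume everyone above a cut-off c is already extubated and has no value, and that nobody dies. With a = (c − μ)/60:
- share lost = 1 − Φ(a)
- mean of those observed = μ − 60·φ(a)/Φ(a)

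For c = 270:
- Control: a = 1.5, mean = 180 − 60 × 0.1295/0.9332 = 171.7
- Warming: a = 0.833, mean = 220 − 60 × 0.2819/0.7977 = 198.8
- Difference: 27.1

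| Cut-off | Lost, control | Lost, warming | Observed difference (true 40) |
|---|---|---|---|
| 300 | 2% | 9% | 32.5 |
| 270 | 7% | 20% | 27.1 |
| 250 | 12% | 31% | 23.2 |

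**Sensitivity to the link between P/F and extubation.** The table assumes that P/F alone decides extubation. In SD units, take a true difference of 0.8 and control extubation of 10% to 20%:
- perfect link: 0.48 to 0.38 observed
- correlation 0.3 to 0.7: between 0.70 and 0.51 observed
- correlation 0: 0.80 observed, so no bias

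With no true effect and equal extubation in the arms, the bias is also zero.

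**Direction.** The sign depends on which arm loses more of which patients. Suppose there is no true effect, the link is perfect, and only the control arm loses its highest 10% or 20%. The control mean then falls by φ(a)/Φ(a) = 0.20 or 0.35 SD, a spurious difference in favour of warming. Deaths remove low values instead, and their rate by arm is not given.

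**Scale against sampling error.** At 10 per arm, the 95% half-width for a mean difference is 1.96 × √(2/10) = 0.88 SD (normal approximation), or about 53 units at SD 60. The shortfalls in the table are 40 − 32.5 = 7.5 to 40 − 23.2 = 16.8 units.

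**The case against.** **Scoring after extubation or death belongs in the SAP.** A condensed article may leave this to the full protocol or SAP, and its absence alone is no finding. The point rests instead on what the article states: fixed P/F times, a data source tied to ventilated care, and an analysis set limited to completers. Followed as written, these three can drop the patients in question.

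**The distortion is small beside the noise.** This is true of any single result at 10 per arm. Random error, however, is visible in a confidence interval and this bias is not, and the estimate is meant to feed a sample size calculation.

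**Extubation benefit is captured elsewhere.** Duration of ventilation and mortality are separate endpoints, so the benefit is not lost to the trial. The P/F estimate is still affected.

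Three stronger readings are tempting, and the documents do not support them.

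- *A reader might infer that the primary endpoint also ceases to exist at extubation.* Sputum is an accepted lower-tract specimen. Sampling may become harder and the specimen type may change, but the endpoint remains. Nor does the article say that P/F is undefined after extubation; it only ties the sampling to ventilated care.
- *A reader might infer that extubation is held back in the warming arm until the device comes out at 72 hours.* No passage says so. Physicians are unblinded and only one arm has a device instruction, so an influence is conceivable, but it is conjecture.
- *A reader might infer that the aim of earlier weaning contradicts the 72-hour device instruction.* An aim and an instruction are not contradictory statements. The mismatch is narrower: one section gives a fixed 72 hours, while two others treat 72 hours as a maximum.

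**Conclusion.** The concern holds for P/F at 48 and 72 hours. Patients extubated or dead before those times may have no value, the loss may depend on treatment, and the completers-only rule does nothing to bring them back.

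Its size cannot be determined from the document. Under the stated illustration (normal P/F, SD 60, true difference 40, deterministic loss above 250 to 300, no deaths), the observed difference is 23 to 32, which is 58% to 81% of the truth. A looser link between P/F and extubation makes the bias smaller, and no link makes it zero. The net direction is unknown, so it should not be said that the plan necessarily understates, or overstates, the effect of warming.

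For viral load the problem is lesser: a possible change of specimen type and timing after extubation. The device-time wording is a separate inconsistency that needs reconciling.

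**What to change.** 1. **P/F at 24, 48 and 72 hours.** For every randomised patient, report by arm how many are extubated alive, ventilated with a P/F, and dead. Add a ranked summary with extubated alive best, ventilated patients ordered by P/F, and dead worst. Show it beside the raw P/F among ventilated patients. The charted data already suffice. The small cost is that ranks are harder to read, and they do not replace the P/F mean and SD needed for planning.
2. **Viral load.** Record specimen type and actual sampling time in both arms. Do not let a sample taken at extubation stand in for the 72-hour value, because that would compare the arms at unequal times.
3. **Device wording.** Reconcile the fixed 72 hours in Intervention regimen with the upper-limit wording in Study intervention and monitoring and in Core temperature modulation, for patients extubated earlier. The clinical rule is for the investigators to choose.

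The changes are wording, one extra table and a simple ranking. No additional patients are needed.

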### Blinding

Due to the nature of this study, the physicians will not be blinded to the randomization assignment, however participants will be blinded. Once a subject is randomized, the research team will receive the randomization assignment (core warming or standard of care) and proceed with the procedures per the assignment.

### Data collection

Demographics (including sex/gender, race, ethnicity, and age via date of birth)Past medical history, social history, physical exam findings and physicians notesConcurrent medicationsPhysical examVital signs: temperature, blood pressure, heart rate, respiration rate, height and weightClinical labs: complete blood count (CBC), chemistry profiles, liver function tests, inflammatory markers (CRP, ferritin), d-dimer, arterial blood gas for determination of PaO2Upper (nasopharyngeal) and lower (tracheal aspirate, sputum) respiratory tract viral load (cycle threshold)

Severity of illness: APACHE III, sequential organ failure assessment (SOFA) scoring systemsVentilator settingsPregnancy test for women of childbearing ageAdverse events or unanticipated problems

Data will be collected via chart review, and is expected to be available from routinely obtained laboratory and vital sign data recorded at routine intervals (i.e., when labs are drawn for routine care in the ICU).

### Schedule of procedures and data collection

**Table pone.0243190.t001:** 

Study Phase	Screening	Randomization/Intervention Phase			Follow- up
Study Days	Day -1 to 0	Day 0	Day 1–2	Day 7, 14	Day 30
Informed Consent	X				
Review Inclusion/Exclusion Criteria	X				
Demographics	X				
Medical History/Interim History*	X		X		X
Physical Examination*	X		X		X
Vital Signs: Temperature, BP, HR, RR*	X		X		X
Height and Weight	X				
Pregnancy Test	X				
Clinical Laboratory Evaluation	X	X	X		
Respiratory tract viral load				X	
Ventilator settings	X	X	X		
APACHE III and SOFA scores	X	X	X		
Clinical Imaging	X	X	X		
Prior/Concomitant Medications	X				X
Randomization		X			
Temperature monitoring		X	X		
PaO2, FiO2, parameter recording		X	X		
Discharge			X		
Adverse Event / Unanticipated Problems Assessment		X	X		X

* Interim medical history, physical exam, and vitals will be collected via chart review from routine clinical care.

### Sample size and power determination

Based on a prior study in patients with sepsis, a maximum temperature of 38.3°C to 39.4°C was associated with survival (aHR 0.61 [95% CI, 0.39–0.99]) [29]. However, the effect of warming specific to COVID-19 patients remains uncertain, and as such, it is not possible to accurately perform a power calculation for this pilot study. It is believed that a total of 10 patients for each group will yield the sufficient pilot data to make an appropriate conclusion regarding the potential utility of core warming in reducing viral load, improving pulmonary physiology, reducing mechanical ventilation duration, and increasing patient survival. It is anticipated that data from this pilot study can be used for planning future larger studies.

### Statistical methods

We will utilize standard measures to report outcomes and measure differences between groups. Specifically, we will use descriptive statistics, including mean (standard deviation) and median (interquartile range). Kaplan-Meier plots of important time to event outcomes and measures will be produced. Normality will be assessed using histograms and the Kolmogorov–Smirnov test. Formal hypothesis testing is not planned for this pilot feasibility study.

### Efficacy analysis

This is a pilot feasibility study to determine the potential role of core warming during COVID-19 treatment.

### Interim safety analysis

All subjects entered into the study and randomized at the baseline timepoint will have detailed information collected on adverse events for the overall study safety analysis. An interim safety analysis will be performed after the first 10 subjects are enrolled in the trial. At this time the safety and tolerability of the study device will be assessed and if deemed safe and appropriate, enrollment will continue to 20 subjects.

### Subject population for analysis

All patients enrolled, randomized to a study arm, and completed in the study will be included for analysis.

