## Methods

This is a single-center pilot study to evaluate if core warming improves respiratory physiology of mechanically ventilated patients with COVID-19, allowing earlier weaning from ventilation, and greater overall survival. The protocol was reviewed and approved by the Institutional Review Board of Washington University. The study is listed on ClinicalTrials.gov with identifier NCT04426344. This prospective, randomized study will include 20 patients diagnosed with COVID-19, and undergoing mechanical ventilation for the treatment of respiratory failure. Patients will be randomized in a 1:1 fashion with 10 patients (Group A) randomized to undergo core warming with an esophageal heat transfer device, and the other 10 patients (Group B) serving as the control group. Patients randomized to Group A will have the esophageal heat transfer device placed in the ICU or other clinical environment in which they are being treated after enrollment and provision of informed consent from appropriate surrogate or legally authorized representative. This study is posted on ClinicalTrials.gov with registration number: NCT04426344. The IRB of Washington University, St. Louis, is performing full review of the final protocol and expected to provide approval; the study will not start prior to IRB approval.

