### Subject recruitment

Subjects will be recruited from the ICU or other clinical environment in which they are being treated (Emergency Department, step-down unit, etc.). Patients will be identified by the PI or other study investigators/coordinators as available. All patients without a DNR order with a diagnosis of COVID-19 and meeting inclusion criteria will be eligible for screening for any exclusion criteria. Written informed consent for the research study will be obtained from patient’s surrogate or legally authorized representative prior to enrollment. If a patient enrolled in the study gains the capacity to consent for him/herself while the study is in progress, the patient will be approached by a study team member and the consent document will be presented directly to the patient. All questions the patient might have will be answered. The patient will be given the opportunity to either withdraw from the study or sign the consent form. The patient will be informed that his or her decision to withdraw from the study will not affect his or her medical care

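### The outcome analysis is limited to randomised patients who 'completed', an undefined post-randomisation condition that can bias the efficacy comparisons in either direction

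*Protocol article*

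**What the plan says.** Under Subject population for analysis, the protocol article states: "All patients enrolled, randomized to a study arm, and completed in the study will be included for analysis". This is the only analysis set that it names for the outcomes.

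Under Total number of subjects and sites it gives two targets. The first is "This single-site study aims to recruit and randomize 20 patients". The second is "It is expected that up to 30 subjects may be consented in order to produce 20 randomized & evaluable subjects".

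Neither 'completed' nor 'evaluable' is defined, and two sections point to different meanings of completion:

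- Intervention regimen: "The device will remain in place until the study is completed (72 hours", which ties completion to the device course.
- Duration of study participation: outcome and ventilation duration are determined at one month after treatment.

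Subject recruitment allows for loss after randomisation when a patient regains capacity: "The patient will be given the opportunity to either withdraw from the study or sign the consent form".

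The safety analysis uses a different set: "All subjects entered into the study and randomized at the baseline timepoint will have detailed information collected on adverse events". The Screening section compares baseline variables by arm for all patients entered.

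**The concern.** Randomisation makes the two arms comparable as assigned. A rule that admits patients by something that happens afterwards can undo this, and the likely reasons for not completing are tied to outcome:

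- **Death** is itself an outcome and a natural reason not to complete.
- **Withdrawal on regaining capacity** is linked to recovery.
- **Early device removal**, on the 72-hour reading, can occur only in the warming arm, because controls have no device course to fail.

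The Blinding section says that physicians are not blinded and that the research team receives the assignment. An undefined 'completed' or 'evaluable' could therefore be judged with the arm known.

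At stake are the effect sizes. The Abstract and the Study endpoints section say that the pilot is to supply estimates for sizing a definitive trial. An estimate from a selected subset would carry its error into that design, and with 10 patients per arm one or two exclusions matter.

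**Working it through.** **Inputs from the article.** Allocation is 1:1 with 10 per arm (Methods). Twenty are to be randomised, from up to 30 consented (Total number of subjects and sites). There is no power calculation (Sample size and power determination) and no formal hypothesis test (Statistical methods), so there is no sample-size formula to reproduce. What can be checked is 10 + 10 = 20, and that 20 from 30 implies a loss of 1 − 20/30 = one third. The text does not say whether that loss falls before or after randomisation.

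**Assumed inputs.** The article gives no planning mortality. For illustration only, take the 28-day mortality of 37.5% and 18.2% that the Introduction cites from prospective data (afebrile patients and their comparison group). Assign 37.5% to control and 18.2% to warming. Let f be the unknown share of deaths left out as non-completers, equal in both arms, with every survivor kept.

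**Mortality among the patients analysed.** With true mortality p, a fraction p(1 − f) are deaths that stay in, and 1 − pf is everyone who stays in. Observed mortality is therefore p(1 − f) / (1 − pf).

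For f = 0.5:

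- Control: 0.375 × 0.5 / (1 − 0.1875) = 0.1875 / 0.8125 = 23.1%.
- Warming: 0.182 × 0.5 / (1 − 0.091) = 0.091 / 0.909 = 10.0%.
- Difference before rounding: 13.1 points.

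| Share of deaths left out, f | Control | Warming | Difference (points) | Expected deaths left out of 10 per arm (control, warming) |
|---|---|---|---|---|
| 0 | 37.5% | 18.2% | 19.3 | 0, 0 |
| 0.25 | 31.0% | 14.3% | 16.7 | 0.9, 0.5 |
| 0.50 | 23.1% | 10.0% | 13.1 | 1.9, 0.9 |
| 0.75 | 13.0% | 5.3% | 7.8 | 2.8, 1.4 |
| 1.00 | 0% | 0% | 0 | 3.8, 1.8 |

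The last row applies only if completion means being alive at the end of follow-up. On the 72-hour reading, deaths after 72 hours stay in and f is below 1 unless every death comes earlier.

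**No true effect, unequal loss.** Let mortality be 37.5% in both arms, with half of the deaths left out in one arm only. That arm shows 23.1% against 37.5%, a spurious difference of 14.4 points. It favours whichever arm lost the deaths, so its sign depends on where the losses fall.

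**Continuous outcomes.** In a simulation with a normal outcome and no true effect, removing the worst 1, 2 or 3 of 10 patients from one arm moved that arm's mean by about 0.17, 0.32 or 0.46 SD. This is an upper case, because it assumes that those lost are exactly the worst on the outcome. If losses are unrelated to arm and outcome, the expected shift is zero.

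**The case against.** The strongest reply is that 'completed' is open. Thirty-day mortality is a listed outcome and Kaplan-Meier plots are planned, so the authors can hardly have meant to remove every death; a death recorded by day 30 may count as completed follow-up. This stands against a stronger inference that a reader might draw, namely that the plan drops all deaths and empties the mortality outcome. It does not rescue the rule, because the two readings of completion select different patients and the article does not choose between them.

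Other inferences are also tempting and are not supported:

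- **Randomised patients are replaced until 20 are evaluable.** The figure of 30 counts patients consented, consent comes before randomisation, and the same section aims to randomise 20. The extra 10 may all be lost before randomisation, which would cause no bias between arms. Replacement after randomisation is neither stated nor ruled out. Nor can one assume both replacement up to 20 and a loss of precision from analysing fewer.
- **Every between-arm comparison is affected.** The safety analysis and the baseline comparison are not limited to completers.
- **The bias flatters warming.** The direction depends on who is lost from which arm. With equal shares of deaths left out, the illustration hides a benefit of warming.
- **The safety section contradicts the analysis population.** Different safety and efficacy sets are common. The contrast shows only that the article names the full randomised set for safety and not for efficacy.

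It can also be said that this is a small pilot without hypothesis tests and that detail may sit in a fuller document. But the article does not leave the population open; it states one. The absence of tests does not protect effect estimates from selection.

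**Conclusion.** The point holds as a fault in a stated rule. The outcome analysis depends on an undefined event after randomisation, and nothing in the article places all randomised patients in the efficacy analysis. This can bias the comparisons of viral load, PaO2/FiO2, ventilation duration, length of stay and mortality, with size and direction unknown in advance.

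Under the assumed mortality rates, the error in the mortality difference runs from none to the whole 19.3 points as the share of deaths left out goes from 0 to 100%. The ends of that range are not forecasts. The figures rest on borrowed rates that are not this trial's planning values, and on equal shares of deaths left out in the two arms.

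**What to change.** 1. In Subject population for analysis, replace the sentence with: *all randomised patients, analysed in the assigned arm regardless of completion, device removal or death*.
2. In Total number of subjects and sites, delete 'evaluable' and state that only consented patients who are never randomised are replaced.
3. Ascertain 30-day vital status from the chart for every randomised patient, unless consent for data use is withdrawn.
4. Report missing 72-hour viral load and PaO2/FiO2 by arm and reason. State how death before 72 hours is handled for these two outcomes, and for ventilation duration and length of stay. Renaming the population does not settle this, since a patient who dies before 72 hours has no 72-hour value.
5. Keep any completer summary as secondary, with 'completed' defined.

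The planned number stays 20, 10 per arm. The article already plans data collection by chart review, so the cost is wording and some extra reporting. The change should be made before data collection starts, because a population rule altered after outcomes are seen would not be credible.
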